## GLOSSARY OF ABBREVIATIONS

|                 |                                                              |
|-----------------|--------------------------------------------------------------|
| AE       | Adverse Event                                         |
| ASR/DSUR | Annual Safety Report / Development Safety Report      |
| BASEC    | Business Administration System for Ethical Committees |
| CRF      | Case Report Form                                      |
| CS       | Caesarean Section                                     |
| CTCAE    | Common Terminology Criteria for Adverse Events        |
| FADP     | Federal Act on Data Protection                        |
| FOPH     | Federal Office of Public Health                       |
| GCP      | Good Clinical Practice                                |
| HRA      | Human Research Act                                    |
| ICH      | International Conference on Harmonisation             |
| ClinO    | Ordinance on Clinical Trials in Human Research        |
| OPTIMAC  | OPTimisation des Mécanismes de l'aCcouchement         |
| SAE      | Serious Adverse Event                                 |

# 1 BACKGROUND AND RATIONALE

Recent data brings out that the CS rate in Switzerland is quite high, reaching 33.4 % (8). Though, the reasons to this increasing amount of CS are not fully known. Therefore, it is absolutely necessary to expand the existing knowledge in different fields, including the biomechanics of childbirth. Numerous CS are performed in response to an obstructed labour, especially when the foetus does not engage in the pelvis near full dilatation. In order to manage such situations, midwives currently position parturients in pragmatic postures. Although not verified by data, this care management suggests that it is possible to impact the position of the bone segments at stake for vaginal birth including pelvis and lumbar spine and to promote the descent of the foetus through the pelvic inlet plane. In his PhD thesis about vaginal birth biomechanics, [name] et al investigated this area and found out that an optimized position similar to the squatting position (hyperflexion of the thighs and loss of the lumbar lordosis) could be close to the perfect delivery position in terms of ability for the foetus to go through the pelvic inlet plane (9). Although these findings are encouraging, it is yet to be confirmed in clinical practice, particularly when a dystocia occurs (10). Prior to doing that, it is though necessary to validate the optimized posture in terms of acceptability in a qualitative clinical study. In this study, fifteen to twenty parturients who respond to the inclusion criteria and whose foetus does not engage in the pelvis near full dilation will be asked to adopt the optimized position for a twenty minutes period. The investigator will then consign information reflecting the progress of the labour on a data sheet. As during labour midwives already position parturients in various postures, some of which very similar to the suggested optimized position, it is sensible to place the study in the risk A category according to ClinO, Art. 61.

## 2 STUDY OBJECTIVES AND DESIGN

### 2.1 Hypothesis and primary objective

The hypothesis is that the optimized birthing position, as described in the first chapter of this protocol, is an acceptable and feasible position. This means that the included parturients will be able to maintain the optimized birthing position for a certain amount of time without giving up or feeling uncomfortable achieving it. The primary objective of the study is thus to determine, by clinically testing the optimized position on a reduced sample of parturients, if it is well accepted by them with a satisfaction scale.

### 2.2 Primary and secondary endpoints

In order to test the hypothesis, the primary endpoint will be whether or not the participants manage to maintain the optimized birthing position for the twenty minutes duration of the study, and if they do, how well they manage it. Some variables like age, parity or history of difficult delivery will be described for each participant. In complement to the primary endpoint, the number of parturients who will refuse to participate to the study will give additional insight into the acceptability of the optimized birthing position. If the reason of their refusal is mentioned, it will then be used to give an additional insight into the acceptability of the optimized birthing position.

The secondary endpoint variables will include:

- General information
- Risk factors of non-engagement of the foetus at full dilation
- Foetal parameters
- Delivery outcome

- Adverse events
- Presence of symphyseal separation

However, this study was not design to obtain significant results regarding the secondary endpoint variables.

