## **2.4 Study intervention**

The intervention will consist in positioning the parturient in an optimized position. It means the parturient will be asked to adopt a supine position with a hyperflexion of the thighs and a flat back, and to maintain the position for twenty minutes. This period of time represents approximately twenty uterine contractions and will give the opportunity to appreciate the effectiveness of the measure without being to constraining for the participants. Most of the time, the patients indeed have epidural anaesthesia and it is though not recommended to make them adopt a position for a prolonged amount of time, in order to avoid any risk of malposition or nerve compression. Help from the investigator or the midwife in charge will be provided if needed or requested. The labour will continue during the twenty minutes period, as obstetrical labour once started can't be interrupted.

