### **4.2. Handling of missing data and drop-outs**

Dropouts will be replaced by recruitment of subsequent new subjects. The data of the participants dropping out from the study before the end of the twenty minutes period will be handled and archived the same as the remaining data. The number of drop-outs will indeed contribute to assess the acceptability of the position.

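### Women who stop early are not distinguished by how long they held the position or why they stopped, although the hypothesis is about holding it for a time

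*Protocol*

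**What the plan says.** The protocol touches this point in five places.

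- **Section 2.1, hypothesis.** Participants "maintain the optimized birthing position for a certain amount of time without giving up or feeling uncomfortable achieving it". The length of time is left open here.
- **Section 2.1, primary objective.** The study is to determine "if it is well accepted by them with a satisfaction scale".
- **Section 2.2, primary endpoint.** The first part is "whether or not the participants manage to maintain the optimized birthing position for the twenty minutes duration of the study". The same sentence continues "and if they do, how well they manage it". The endpoint thus has a yes/no part for everyone and a graded part for completers.
- **Section 2.4.** Women are asked "to maintain the position for twenty minutes". The section also argues against a prolonged hold, given that most patients have epidural anaesthesia, "in order to avoid any risk of malposition or nerve compression".
- **Section 4.2.** Data from women "dropping out from the study before the end of the twenty minutes period" are kept and handled like the rest, and the count of drop-outs is used to judge acceptability. Drop-outs are replaced.

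Section 3.4 lists the grounds for withdrawal: withdrawn consent, disease progression, a foetal cardiac rhythm disorder, or progress of labour. No section names minutes held, time of stopping or reason for stopping as an endpoint or a recorded variable.

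**The concern.** The women who do not reach twenty minutes say most about the limits of acceptability, and the endpoint describes them least. Completers receive a grading. A non-completer contributes a failure on the yes/no part and one unit in the drop-out count. Nothing in the stated endpoint separates a woman who gives up almost at once from one who nearly finishes.

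It also does not separate a woman who gives up because the position is uncomfortable from one who is withdrawn because labour has progressed or the foetal heart rhythm is disturbed. Under 4.2 all of them would add to a count that is read as evidence on acceptability, yet progress of labour is a favourable event.

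The background section says acceptability must be established before the position is tested for effect, and 6.1 calls this study a first step. Whoever plans the next step would want to know whether non-completion meant immediate rejection, near-completion, or an obstetric event. If the times and reasons are not noted at the bedside, they cannot be recovered after the labour.

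**Working it through.** The protocol gives no alpha, power, effect size or calculated sample size (4.1 says none was defined), so there is no figure to reproduce. The check has two parts.

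**1. What the text distinguishes.**

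| Woman | Yes/no part (2.2) | Graded part (2.2) | Drop-out count (4.2) |
|---|---|---|---|
| Completes twenty minutes | Yes | Applies | Not counted |
| Gives up at minute 1 | No | Does not apply | Counted |
| Gives up at minute 19 | No | Does not apply | Counted |
| Withdrawn for labour progress (3.4) | No, or unscored | Does not apply | Counted, on the text as written |

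The second and third rows are identical. The last row differs at most in whether the yes/no part is scored, which the protocol does not settle.

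**2. Size, by illustration.** The hold period of 20 minutes is from 2.4. The number of women is 20 (3.1); section 1 gives fifteen to twenty. The numbers and times of early stops are assumptions.

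Write n for the women positioned, c for completers, and t for the minute at which all n − c others stop.

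- Completion = c / n, with an exact (Clopper-Pearson) 95% interval.
- Mean minutes held, up to 20 = (20c + t(n − c)) / n.

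With n = 20 and c = 12:

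- Completion = 12/20 = 60%, 95% CI 36.1% to 80.9%, whatever the value of t.
- t = 2: (240 + 16)/20 = 12.8 minutes.
- t = 18: (240 + 144)/20 = 19.2 minutes.
- Difference: 6.4 minutes, with the same completion result.

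Other assumed counts, with stops at minute 1 or minute 19:

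| n | Early stops | Completion (95% CI) | Mean held, t = 1 | Mean held, t = 19 |
|---|---|---|---|---|
| 20 | 1 | 95% (75.1% to 99.9%) | 19.05 | 19.95 |
| 20 | 3 | 85% (62.1% to 96.8%) | 17.15 | 19.85 |
| 20 | 5 | 75% (50.9% to 91.3%) | 15.25 | 19.75 |
| 15 | 1 | 93.3% (68.1% to 99.8%) | 18.73 | 19.93 |
| 15 | 3 | 80% (51.9% to 95.7%) | 16.20 | 19.80 |
| 15 | 5 | 66.7% (38.4% to 88.2%) | 13.67 | 19.67 |

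The loss grows with the number of early stops and is small if almost everyone completes.

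**Precision.** The standard error of the completion proportion at 60% is √(0.6 × 0.4 / 20) = 0.110. In simulation with a constant stopping rate it was 0.109 from the yes/no result and 0.108 from times. Recording time does not make the completion estimate more precise.

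**The case against.** The strongest reply is that the study is not about duration. The objective is acceptance on a satisfaction scale, 2.4 fixes the open-ended time of the hypothesis at twenty minutes and gives reasons, and completing a manoeuvre of fixed length is a legitimate feasibility endpoint. This stands. It means the endpoint should stay, and three stronger readings should be set aside.

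- *A reader might infer that the plan reduces the hold to pass or fail.* It does not. Completers are graded, and the objective names a satisfaction scale.
- *A reader might infer that the study cannot say how long the position is tolerable.* That goes too far. The longest tolerable time is not a stated aim, and completers are observed only to twenty minutes in any case. The data of early stoppers are kept, and neither the CRF nor any SAP is shown, so recording of stop times can be neither confirmed nor excluded.
- *A reader might infer that minutes held should replace completion as the primary measurement.* The withdrawals in 3.4 speak against this. A short time caused by progress of labour or a foetal rhythm disorder would be read as poor tolerance. A mean of 19.2 minutes would also look nearly perfect with 40% not completing.

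It can also be said that the contrast between minute 2 and minute 18 is extreme, and that tabulating stop times belongs in an SAP. The first is fair; the figures show what the endpoint cannot separate, not what is expected. The second holds only if the times are collected. The endpoint and the use of drop-outs are fixed in the protocol, and an SAP cannot analyse what was not written down during labour.

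**Conclusion.** The point holds in a limited form. As specified in 2.2 and 4.2, non-completers are not distinguished by how long they held the position or by why they stopped, while the hypothesis in 2.1 concerns holding it for a time. With 12 of 20 completing, the same 60% is compatible with a mean hold of 12.8 or 19.2 minutes. That range rests on assumed counts and on all early stops falling at one minute. With a single early stop among 20 (minute 1 or minute 19) the gap is 0.9 minutes.

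This is an inexpensive improvement to the description of non-completers. It does not show that the completion endpoint is wrong. If the CRF already holds the times and reasons, what remains is to name them in the protocol.

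**What to change.** Keep the twenty-minute completion endpoint, the grading for completers and the satisfaction scale. Then:

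1. In 2.2, add that clock start time, clock stop time and the reason for stopping are recorded for every woman positioned, and that minutes held support the primary endpoint as a description.
2. In 4.2, add that minutes held are listed individually for each non-completer with the reason, alongside the number of drop-outs.
3. In the same listing, show stops for progress of labour or foetal cardiac rhythm disorder separately from giving up or discomfort, so that the former are not read as poor acceptance.

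With fifteen to twenty women, an individual listing is enough. The change leaves the position, the hold period and the withdrawal rules as they are.

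Cost: two time fields and one reason field on the CRF, a sentence or two in each of the two sections, and a small amount of tabulation. No further participants or procedures are needed.

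### The primary endpoint names neither the satisfaction scale nor comfort, and it grades only women who complete twenty minutes, so women who give up are counted but never rated

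*Protocol*

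**What the plan says.** Protocol section 2.1 states the primary objective as finding out "if it is well accepted by them with a satisfaction scale". Its hypothesis is that women will be able to "maintain the optimized birthing position for a certain amount of time without giving up or feeling uncomfortable achieving it".

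Protocol section 2.2 gives the primary endpoint, introduced as the means of testing that hypothesis, in two parts. The first applies to everyone: "whether or not the participants manage to maintain the optimized birthing position for the twenty minutes duration of the study". The second follows in the same sentence: "and if they do, how well they manage it". Refusals to take part, with reasons where given, are added as further information. The satisfaction scale and comfort appear in neither the primary nor the secondary list.

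Protocol section 4.2 deals with women who stop early. "Dropouts will be replaced by recruitment of subsequent new subjects". Their data "before the end of the twenty minutes period will be handled and archived the same as the remaining data", and "The number of drop-outs will indeed contribute to assess the acceptability of the position". Section 3.4 likewise keeps and uses whatever data are available from withdrawn women. It lists withdrawal of consent, disease progression, foetal cardiac rhythm disorder and labour progression as reasons for withdrawal.

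**The concern.** The objective, the hypothesis and the endpoint should describe the same quantity, and here they do not. The instrument that defines the objective is mentioned once, in section 2.1. It has no endpoint and no time of administration in sections 2.2 or 3.3. Comfort is half of the hypothesis but is not named in the endpoint; at best it is implied by an undefined judgement of how well a woman managed.

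That judgement is asked for only after a completed twenty minutes. Women who stop early are plausibly the least satisfied, and theirs are the ratings the endpoint does not request. Acceptability is the purpose of the study, and a rating not taken at the time cannot be recovered by a later analysis.

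**Working it through.** The protocol gives no success threshold, alpha, power or expected rate, and section 4.1 defines no sample size. There is no figure to reproduce. The check is a comparison of texts, followed by an illustration of size.

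**Texts side by side**

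| Element | Section 2.1 | Section 2.2 | Who contributes under 2.2 |
|---|---|---|---|
| Holding the position | Yes, duration unspecified | Yes, twenty minutes | All participants |
| Comfort | Yes ("without giving up or feeling uncomfortable achieving it") | Not named | Completers at most, if managing well includes comfort |
| Satisfaction scale | Yes | Not named | Not stated |
| How well managed | Not mentioned | Yes | Completers only |

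A woman who stops at, say, ten minutes is a failure in the first row and adds to the drop-out count of section 4.2. No rating is requested from her in any row. The promise in sections 3.4 and 4.2 to keep her data covers what has been collected and does not create a rating that was never asked for.

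**Illustration 1: 20 women start, no replacement**

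Inputs: 20 starters (section 3.1; section 1 says fifteen to twenty). The number k who give up is an assumption, as is the premise that every completer rates the position well. Held proportion = (20 − k)/20. Completer-only grade = (20 − k)/(20 − k). Intervals are exact (Clopper-Pearson) 95%.

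| k | Held, all starters | Completer-only grade |
|---|---|---|
| 2 | 18/20 = 90% (68.3 to 98.8) | 18/18 = 100% (lower limit 81.5) |
| 5 | 15/20 = 75% (50.9 to 91.3) | 15/15 = 100% (lower limit 78.2) |
| 8 | 12/20 = 60% (36.1 to 80.9) | 12/12 = 100% (lower limit 73.5) |

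The yes/no part falls as women give up. The graded part stays at 100%.

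**Illustration 2: drop-outs replaced until 20 complete**

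This reading of section 4.2 is an assumption, since the protocol does not say when replacement stops. Starters = 20 + k.

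| k | Completer-only grade | Held and rated well, all starters |
|---|---|---|
| 2 | 20/20 = 100% (lower limit 83.2) | 20/22 = 91% (70.8 to 98.9) |
| 5 | 20/20 = 100% (lower limit 83.2) | 20/25 = 80% (59.3 to 93.2) |
| 8 | 20/20 = 100% (lower limit 83.2) | 20/28 = 71% (51.3 to 86.8) |

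With replacement, the graded result is the same whether 2 or 8 women gave up. In the row with k = 5, acceptance among all starters lies between 20/25 = 80%, if none of the five would have rated the position well, and 25/25 = 100%, if all would have. Without ratings from those five women the study cannot say where in that range it falls.

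**The case against.** Several points on the other side are sound.

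- A reader might infer that women who gave up never enter the acceptability result. The documents do not support that. They are failures in the first part of the section 2.2 endpoint, and section 4.2 expressly uses their number. What they lack is a rating.
- A reader might infer that a woman who holds for twenty minutes in marked discomfort is a success under 2.2 and a failure under 2.1. Section 2.2 defines no success category, and the wording on how well she managed could take in discomfort among completers. This stands, but the term is undefined and could equally mean technique or need for help.
- A reader might infer from the loose duration in 2.1 that no result could refute the hypothesis. That goes too far: sections 1, 2.2, 2.4 and 4.2 all say twenty minutes, and many women giving up would plainly count against the position.
- Nothing says that the satisfaction scale itself is confined to completers. Section 2.1 applies it to the sample as a whole, and a case report form not shown may schedule it for everyone. This also stands. The restriction lies in the graded clause of the endpoint, and the scale's place is simply unstated.
- The study is a qualitative pilot, and scoring rules can be left to an analysis plan. That is fair for cut-offs and summaries, and it is a good reason not to impose numerical success bars, which would have no basis in the protocol. It does not extend to which measure is primary and from whom it is collected, because that governs what is recorded in the labour ward.

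**Conclusion.** The point holds as a mismatch between objective and endpoint, together with a graded component conditional on completion. Section 2.1 promises a satisfaction scale and freedom from discomfort; section 2.2 names neither and asks for a grade only from completers. Women who give up contribute a count and no rating, and replacement can fill the graded group wholly with completers.

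The size depends on how many give up, which the protocol does not predict. If every completer rates the position well and recruitment continues to 20 completers, 2, 5 or 8 replaced drop-outs leave the grade at 100%, against 91%, 80% or 71% of starters known to have held and accepted the position. These are illustrations under stated assumptions, not forecasts. The yes/no part of the endpoint does not share this selection, provided that replaced women stay in its denominator.

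**What to change.** In section 2.2:

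- Name the satisfaction scale, with an item on comfort, as a primary measure beside holding the position for twenty minutes.
- Collect it from every woman who starts the position, at twenty minutes or soon after she stops.
- Report both measures over all starters, with replaced drop-outs kept in the denominator.
- Record why each woman stopped, and report stops for labour progression, foetal cardiac rhythm disorder or another reason listed in section 3.4 separately from giving up. Otherwise women who did not reject the position would be counted as if they had.

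In section 2.1, state the twenty minutes already used elsewhere in the protocol, for consistency.

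The cost is a few sentences in 2.1 and 2.2 and one short rating from women who stop early. The acceptability result may be less favourable than a completer-only grade, and some women may be unable or unwilling to answer; their number should be reported.

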# **3 STUDY POPULATION AND STUDY PROCEDURES**

## **3.1 Inclusion and exclusion criteria, justification of study population**

The study population will be constituted of twenty parturients with interrupted labour due to the non-engagement of the foetus in the pelvis at full dilation. Only the parturients responding to the inclusion criteria will participate to the study.

Study inclusion criteria:

- Informed consent as documented by signature
- Parturient in situation of mechanical dystocia (non engagement at full dilation)

Study exclusion criteria:

- Inability or medical contraindications to undergo the investigated intervention (e.g. orthopaedic injury or disease preventing the parturient from adopting the optimised position)
- Clinically significant concomitant diseases
- Incapacity of judgment
- Inability to follow the procedures of the study due to language problems, psychological disorders, dementia, etc.
- Foetus cardiac rhythm disorder

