## **3.2 Recruitment, screening and informed consent procedure**

The recruitment of the participants will begin by information during the antenatal consultation in the CHUV polyclinic of gynaecology and obstetrics. The patients will receive the participant information sheet and oral information from the physician in charge or from the co-investigator accompanied by a physician. If they are willing to participate to the study, they will have to sign

the consent form directly at the end of the consultation.

The physician or the co-investigator will explain to each patient the nature of the study, its purpose, the procedures involved, the expected duration, the potential risks and benefits and any discomfort it may entail. Each participant will be informed that the participation in the study is voluntary and that she may withdraw from the study at any time and that withdrawal of consent will not affect her subsequent medical assistance and treatment, or the medical assistance of the foetus.

The participant will be informed that authorised individuals other than their treating physician, including the project leader ([name]), her research assistant ([name]) and the co-investigator ([name]), may examine her medical records.

All participants for the study will be provided a participant information sheet and a consent form describing the study and providing sufficient information for participant to make an informed decision about their participation in the study. A frame of twenty minutes will be given to the parturient in order to decide whether or not she will participate to the study.

The consent form will be signed and dated by the participant and a physician. All the consent forms will be signed during the consultation preceding the admission in the labour ward. A copy of the signed informed consent will be given to each study participant. The consent form will be retained as part of the study records. The informed consent process will be documented in the patient file and any discrepancy to the process described in the protocol will be explained.

At the admission in the labour ward, an oral confirmation of the informed consent will be asked in presence of the co-investigator and the midwife to make sure the parturient still wants to participate to the study.

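### The refusal count read as acceptability comes from women asked before dystocia is known, and it has no denominator

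*Protocol*

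**What the plan says.** Section 2.1 ties acceptability to the women included: whether they can keep the position for a time without giving up or being uncomfortable. The primary endpoint in 2.2 follows from this, namely whether participants hold the position for twenty minutes and how well they manage.

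Section 2.2 then adds a second source of evidence: "the number of parturients who will refuse to participate to the study will give additional insight into the acceptability of the optimized birthing position". On reasons it says: "If the reason of their refusal is mentioned, it will then be used to give an additional insight".

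Section 3.2 sets the timing. "The recruitment of the participants will begin by information during the antenatal consultation", and "All the consent forms will be signed during the consultation preceding the admission in the labour ward". A second contact follows: "At the admission in the labour ward, an oral confirmation of the informed consent will be asked".

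Section 3.1 describes the study population as "twenty parturients with interrupted labour due to the non-engagement of the foetus in the pelvis at full dilation".

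Section 4.2 treats early stopping as evidence too: "The number of drop-outs will indeed contribute to assess the acceptability of the position". Section 3.4 lists withdrawal of consent together with withdrawals for disease progression, foetal heart-rhythm disorder and progress of labour.

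**The concern.** Section 2.2 gives the number of refusals a specific meaning, insight into how acceptable the position is. The women who can produce that number under 3.2 are not yet known to belong to the population in which acceptability is to be judged. They are asked whether they would join a study should a complication occur. A refusal may express a view of the position, but it may equally express reluctance to take part in research or to make a decision in advance.

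The sentence also asks for a number and does not say out of how many. Such a number rises with recruitment effort even if every woman's opinion stays the same. In a study of about twenty participants, a large count could colour the reading of acceptability without bearing much on it.

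**Working it through.** There is no figure in the protocol to reproduce: section 4.1 defines no sample size, and no refusal rate or rate of non-engagement is given. The only rate is the 33.4% caesarean rate in section 1, which covers all causes. The check is therefore the order of events, followed by an illustration on assumed values.

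**Order of events**

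1. Antenatal consultation (3.2): information is given and the form is signed. Refusal is possible. Eligibility is unknown.
2. Labour-ward admission (3.2): consent is confirmed orally. Refusal is possible. Nothing ties this moment to full dilation, so eligibility is in general still unknown.
3. Non-engagement at full dilation (3.1): the woman becomes eligible and is asked to adopt the position (2.4).
4. The twenty minutes: stopping early is a drop-out (4.2).

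Both points at which 3.2 asks for agreement precede step 3. Neither 2.2 nor 3.2 says how to count a woman who declines at step 3, before the twenty minutes begin.

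**How the count behaves**

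Assumptions: N = 20 participants (section 3.1; section 1 says fifteen to twenty); r = share refusing antenatally; d = share of consenting women who become eligible and take part; refusal unrelated to later dystocia; admission refusals ignored.

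- Consents needed = N/d
- Refusals = (N/d) × r/(1 − r)
- Refusers who would later have become eligible = d × refusals = N × r/(1 − r)

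| d | Consents (20/d) | Refusals, r = 10% | Refusals, r = 20% | Refusals, r = 30% |
|---|---|---|---|---|
| 20% | 100 | 11 | 25 | 43 |
| 10% | 200 | 22 | 50 | 86 |
| 5% | 400 | 44 | 100 | 171 |
| 2% | 1000 | 111 | 250 | 429 |
| Would have become eligible, any d | – | 2.2 | 5 | 8.6 |

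Three things follow.

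- At r = 20% the count moves from 50 to 250 as d falls from 10% to 2%, a factor of five with unchanged attitudes. Only 5 of those refusers would have reached the target situation in either case.
- Nearly the same count, 43 or 44, arises from 30% refusal with d = 20% and from 10% refusal with d = 5%. The count alone cannot tell these apart.
- Dividing by the number asked removes this problem: 50/250, 100/500 and 250/1250 are all 20%. It does not remove the other one, that the 20% describes women asked before dystocia is known.

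With 15 participants every count is multiplied by 15/20 = 0.75, and the pattern is the same.

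**The case against.** The strongest reply is that the protocol claims little for this number. It complements the primary endpoint, no decision rule depends on it, and reasons for refusal will be used, which is a natural tool in a study described as qualitative. Consent forms are retained and the consent process is documented in the patient file (3.2), so the antenatal denominator can largely be rebuilt. The word parturients in 2.2 might point to women at admission. A statistical analysis plan, not available here, may define the stages.

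Much of this stands and limits the point to supporting evidence. It does not remove it. Reasons are used only if mentioned, so they separate the two kinds of refusal only partly. Section 3.2 also uses the word parturient for the woman deciding on consent, so the term does not settle the stage, and admission too comes before eligibility is established. An analysis plan cannot recover the number asked at each stage if it was never logged.

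Two stronger readings are not supported.

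- A reader might infer that the informative refusals, by women already in dystocia, are lost among the drop-outs. Section 4.2 expressly counts drop-outs toward acceptability, and 3.4 does not say that a woman declining at that moment is left out of the refusal count. Her classification is unstated; she is not shown to be hidden.
- A reader might divide refusals by refusals plus participants and quote the resulting high percentage as the error. The protocol proposes no such ratio, so no percentage distortion can be attributed to it.

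**Conclusion.** The point holds as a modest one. Followed as written, the refusal count reflects how many women were approached and how willing they were to join research, more than acceptance of the position by women with non-engagement at full dilation. This rests on the sequence in 3.2 and 3.1 and on the missing denominator in 2.2, not on any assumed rate. It does not require that most women approached never become eligible, though that would follow for any eligibility share below one half if refusal is unrelated to later dystocia.

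The size cannot be fixed from the protocol. The fivefold range shown depends on the assumed refusal and eligibility shares and only illustrates the direction. The primary endpoint is not affected. A correction is worth making because it is cheap and has to be in place before recruitment.

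**What to change.** In sections 2.2 and 3.2, provide for refusals to be recorded at three stages, each with the number of women asked and any reason given:

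1. at the antenatal consultation;
2. at the oral confirmation on admission;
3. once the woman is eligible and is offered the position.

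Report stages 1 and 2 mainly as recruitment feasibility. Refusals at those stages that a woman explicitly attributes to the position can be described separately, since they still carry some information.

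Base the acceptability statement on stage 3, as refusals out of eligible women offered the position. Show it separately from the drop-outs already counted under 4.2, and from withdrawals under 3.4 for foetal rhythm disorder or labour progression. State in which category a woman belongs who declines at stage 3 before the twenty minutes start.

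The cost is a simple screening log and a few sentences of protocol text. No study procedure, endpoint or participant number changes.
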